## Abstract

**Methods::**

This trial is a single-center, randomized, assessor-blinded, controlled clinical study. We will recruit 40 patients with POP and assign them to the control group and the experimental group in a 1:1 ratio according to the intended protocol. The control group received 24 weeks of conventional medication and health promotion, and the experimental group received 24 weeks of personalized exercise prescription intervention (Yijinjing, treadmill exercises, and strength training). Outcome measures include pain (visual analogue scale), muscle strength (bilateral upper limb grip strength and isometric muscle strength of the trunk, hip, and knee), balance (Balance test with eyes open and closed while standing on one leg), and BMD (Lumbar spine 2–4 and femoral neck). In addition, bone metabolism indicators include parathyroid hormone, osteocalcin, 25-hydroxyvitamin D3 (1,25(OH) 2D3), type I procollagen aminoterminal peptide and type I collagen carboxy-terminal peptide. Outcome measures will be assessed before and after 24 weeks of intervention. Statistical analysis was performed by SPSS22.0.

**Discussion::**

This trial aimed to enrich the content and form of exercise rehabilitation prescriptions for patients with POP, which is conducive to improving the exercise rehabilitation effect and quality of life in this population.

## 1. Introduction

Primary osteoporosis (POP) in clinical practice refers to a systemic bone disease typically characterized by reduced bone mass and microstructural damage to bone tissue, mostly in middle-aged and elderly people.^[1]^ Its symptoms include low back pain, shortening of body length, fracture, and decreased respiratory function, which seriously reduces the quality of survival of patients.^[2]^ Currently, pharmacological interventions are still the most common treatment for POP, however, long-term drug use is costly and has the potential risk of increasing the occurrence of various adverse effects.^[3]^ Therefore, it is crucial to explore safer and more efficient alternative therapies. Previous studies have shown that regular exercise can effectively enhance BMD and reduce the incidence of osteoporosis (OP) in middle-aged and elderly people with a high safety profile.^[4,5]^ The development of an accurate and appropriate exercise prescription has been of great interest to medical staff and patients as a relatively economical, efficient, and safe treatment method in the clinical treatment of POP.^[6]^

As a specific traditional sport in China, traditional Chinese health-preservation exercises are rich in form and easy to accept the load, making them more suitable for middle-aged and elderly people to participate.^[7]^ In our previous study, we found that Yi Jin Jing was optimal in improving pain, bone density, and bone formation in POP patients compared with TaiChi, Ba Duan Jin, and Wu qin xi through a network Meta-analysis.^[8]^ Therefore, Yi Jin Jing may be preferred in clinical practice. In addition, treadmill exercises and strength training have been shown in the literature to have significant effects on the improvement of BMD and bone metabolism.^[9,10]^ However, previous exercise protocols have some limitations. First, most of the studies were very vague in setting and monitoring the exercise intensity, and failed to make individualized exercise intensity programs according to the patient’s physical condition, which may lead to the intervention effect not achieving the expected effect and even causing secondary injuries. Second, the single and poorly targeted intervention means are more prominent, which will directly lead to lower patient compliance and difficulty in completing rehabilitation training. Finally, current assessments of POP focus on changes in bone mineral density (BMD), ignoring factors such as muscle strength and physical function. Previous studies have also shown that the decline of the skeletal muscular system in patients with POP causes muscle atrophy and bone loss, which in turn causes loss of muscle strength, decreased motor ability and balance, and increases the risk of falls, ultimately leading to a reduced quality of life.^[11,12]^

Therefore, this trial proposes to establish a personalized exercise prescription based on Yi Jin Jing and combined with treadmill exercises and strength training, and then observe its effects on pain, muscle strength, balance, bone density, and bone metabolism indexes in POP patients. The aim of this study is to enrich the content and form of exercise rehabilitation prescriptions for POP patients, to improve the effect of exercise rehabilitation in this population, and to improve the quality of life.

## 2. Methods

### 2.1. Study design

This trial is a single-center, randomized, assessor-blinded, controlled study. We will recruit 40 POP patients and assign them to the control group (conventional medication and health education) and the experimental group (personalized exercise prescription based on Yijinjing) in a 1:1 ratio according to the intended protocol. Before randomization, all patients were required to sign an informed consent form. The flow chart of the study is shown in Figure 1. the study protocol is based on the SPIRIT reporting guidelines, where the SPIRIT figure (schedule of enrollment, interventions, and assessments) is shown in Figure 2, and the checklist is shown in Supplementary Material 1 (http://links.lww.com/MD/I526). The study started in November 2022 at Guizhou Provincial Orthopedics Hospital and is expected to end in October 2023.

**Figure 1. F1:**
[figure not shown]
Flow chart of the study.

**Figure 2. F2:**
[figure not shown]
SPIRIT figure as recommended by 2013 SPIRIT statement.

### 2.2. Clinical registration and ethical approval

This study complied with the Declaration of Helsinki and was approved by the Ethics Committee of Guizhou Provincial Orthopedics Hospital (approval number: LW2021101401). In addition, this study was also registered with the Chinese Clinical Trials Registry under the registration number ChiCTR2200056780.

### 2.3. Inclusion criteria

Included patients will meet the diagnostic criteria of the guidelines for the diagnosis of POP (2017).^[13]^Bone density test T value ≤ −2.5 and moderate pain in the low back (3 < visual analogue scale score < 7).Age between 50 and 75 years old, male and female gender was not limited.Signed informed consent and good compliance.

### 2.4. Exclusion criteria

Secondary OP and other causes of OP.Combined bone diseases such as bone tuberculosis and malignant bone tumor.Severe abnormalities in cardiovascular, liver, kidney, stomach, and other system functions.Persons with cognitive dysfunction or mental illness.Those who have received medication and regular exercise in the past 3 months.Those who cannot tolerate exercise.

### 2.5. Sample size estimation

Sample size estimation was performed by G.power3.1. Statistical efficacy analysis was performed based on a previous study.^[14]^ A two-sided test was selected, α was set to 0.05, Statistical power was set to 0.8, and the sample size estimation resulted in 34 participants. Considering a 20% dropout rate, the finalized sample size was 40 individuals.

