### 2.6. Randomization, concealment, and blinding

A random sequence will be generated by SPSS 22.0, and patients will be randomly assigned to experimental and control groups based on a 1:1 ratio. The randomization grouping results will be stored in opaque, sealed envelopes with serial numbers marked on the cover. These envelopes were opened only before the official start of the intervention.

Blinding of therapists and patients is not possible due to the limitations of the intervention method. Data collection was performed and recorded by specialized personnel, and data analysis was performed by an independent statistician. The grouping of patients was not known for the above population.

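### The 34 needed, the 20% dropout and the 40 enrolled do not agree: 40 patients leave 32 evaluable, two short, and cover only 15% dropout

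*Protocol article*

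**What the plan says.** Section 2.5 sets out the calculation in a few lines. The design inputs are "A two-sided test was selected, α was set to 0.05, Statistical power was set to 0.8". The result is that "the sample size estimation resulted in 34 participants". The allowance for loss follows: "Considering a 20% dropout rate, the finalized sample size was 40 individuals". For the effect size the section points to an earlier study ("Statistical efficacy analysis was performed based on a previous study") and gives no value. It does not name the outcome or the test used for the calculation.

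Section 2.6 states that "patients will be randomly assigned to experimental and control groups based on a 1:1 ratio", so 34 means 17 per arm and 40 means 20 per arm. The abstract and section 2.1 repeat the total of 40. No other section gives a different dropout rate or sample size. Section 2.8 places outcome measurement at baseline and at the end of treatment only, and section 2.9 compares the arms with an independent-samples t test when the data are normal.

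**The concern.** A dropout allowance exists so that the number left at the end still meets the number the power calculation asked for. Here it does not: the stated loss applied to the stated enrolment leaves fewer patients than the stated requirement. At most two of the three figures can stand together.

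The loss matters in this design because there is no intermediate visit. A patient who leaves before week 24 has no post-baseline value and cannot contribute to the planned t tests. The evaluable number is therefore the number on which the 80% depends. A reader who later interprets the trial's result will take from section 2.5 that 80% power was protected against 20% dropout, and the design does not give that protection.

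**Working it through.** **Inputs from the article:** required total 34, power 0.80, two-sided alpha 0.05, dropout 20%, final total 40 (all section 2.5); allocation 1:1 (section 2.6); between-arm comparison by independent-samples t test (section 2.9). **Not given:** effect size or standard deviation. The dropout arithmetic does not need them; the power figures below do, and rest on an assumption.

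**Step 1: can 40 be reproduced?**
- Correct inflation, N/(1 − dropout): 34/0.80 = 42.5, so 43, or 44 to keep equal arms. This does not give 40.
- Common shortcut, N × (1 + dropout): 34 × 1.20 = 40.8, which rounds up to 41. Forty is consistent with this shortcut rounded down, although the article does not say how it was obtained.

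**Step 2: what does 40 deliver?**
- Evaluable at 20% dropout: 40 × 0.80 = 32, or 16 per arm if losses are equal. Shortfall: 34 − 32 = 2.
- Largest dropout that still leaves 34: 1 − 34/40 = 0.15.
- Check on nearby totals: 42 × 0.80 = 33.6 (too few), 43 × 0.80 = 34.4, 44 × 0.80 = 35.2.

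**Step 3: what is the loss in power?** Assume that the calculation was a two-sample t test and that 34 is the smallest 1:1 total reaching 80%. With n per arm and standardised difference d, power comes from the noncentral t distribution with 2n − 2 degrees of freedom and noncentrality d × √(n/2). Solving for 80% gives d = 0.991 at 17 per arm and d = 1.024 at 16 per arm. If d were 1.024 or more, 32 would already have been enough, so d must lie between these values.

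| d | 34 evaluable | 32 evaluable | 40 evaluable (no loss) |
|---|---|---|---|
| 0.991 | 80.0% | 77.4% | 86.3% |
| 1.007 | 81.3% | 78.7% | 87.4% |
| just under 1.024 | 82.5% | just under 80% | 88.4% |

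The largest shortfall from the stated 80% is 80.0 − 77.4 = 2.6 points. The normal approximation gives nearly the same at the lower end (77.6%). Unequal loss changes little: 17 and 15 per arm give 77.2% at d = 0.991.

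**The case against.** The strongest reply is that the consequence is slight. Two evaluable patients are missing, power falls by at most about 2.6 points, and the shortfall arises only if dropout exceeds 15%. Nothing in the analysis or the conduct of the trial changes, and a null result read at 77% to 80% power means much the same as one read at 80%. All of this stands, and it limits how serious the point can be. It does not reconcile the figures. Nor can the inconsistency be put down to the brevity of a journal article: the inputs and the result are printed, and the result does not follow from them.

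A reader might go further and infer that 34 came from a paired, single-group calculation, so that power for the comparison between arms is far below 80%. It is true that a paired t test at a standardised change of 0.5 also gives 34 (power 0.795 at 33 and 0.808 at 34). But section 2.5 mentions neither a paired test nor that effect size, and agreement on one integer does not identify the set-up. A two-group, two-time repeated-measures interaction with f = 0.25 and correlation 0.5 gives 34 as well (0.781 at 32, 0.807 at 34), and that is a between-group comparison. The article does not support choosing one of these over another, so no claim of grossly inadequate power follows.

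**Conclusion.** The inconsistency is real and rests only on the article's own 34, 20% and 40: at the stated dropout, 40 patients leave two fewer than the stated requirement, and the allowance actually made is 15%. Provided that 34 is the smallest 1:1 total reaching 80%, 32 is below 80% whatever the effect size.

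The size of the loss, 77.4% to just under 80% power, is conditional. It assumes a two-sample t test, equal loss in the two arms and a back-solved standardised difference of about 0.991 to 1.024. The sponsor's actual effect size would replace this range with a single figure. Severity is minor to moderate: this is a wrong statement about the design that should be corrected, and it is not evidence that the trial is materially underpowered.

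**What to change.** Restate the sentence in section 2.5 so that its figures agree, in one of two ways:

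- say that 40 patients allow for 15% dropout while keeping 34 evaluable; or
- keep the 20% dropout and state the power for 32 evaluable patients, computed from the effect size the sponsor used. The back-solved range above should not be printed in place of that calculation.

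Either change costs one sentence and a slightly less favourable figure. No extra enrolment is required. Should the sponsor prefer to keep both 80% power and 20% dropout, the matching total is 43, or 44 at 1:1, which is three or four more patients.

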### 2.6. Randomization, concealment, and blinding

A random sequence will be generated by SPSS 22.0, and patients will be randomly assigned to experimental and control groups based on a 1:1 ratio. The randomization grouping results will be stored in opaque, sealed envelopes with serial numbers marked on the cover. These envelopes were opened only before the official start of the intervention.

Blinding of therapists and patients is not possible due to the limitations of the intervention method. Data collection was performed and recorded by specialized personnel, and data analysis was performed by an independent statistician. The grouping of patients was not known for the above population.

### 2.7. Intervention method

The control group will be given conventional medication and health education. The patients will be advised to take a calcium supplement, Calcium Carbonate and Vitamin D3 Granules (Beijing, China), which contains 500 mg of calcium and 200 IU of vitamin D in one sachet twice a day for 24 weeks. Health education includes informing patients about the dangers of OP, maintaining a good lifestyle and diet, and taking their medication on time.

#### 2.7.1. Experimental group.

In addition to conventional medication and health education, the experimental group will be given Yi Jin Jing exercise, treadmill exercises and strength training. Patients will wear Polar heart rate belt during training, and the rehabilitation therapist will monitor the patients’ exercise in real-time through the heart rate bands and make an immediate assessment of the patient’s fatigue level according to the Borg scale. Patients should stop the training immediately if they showed chest tightness, shortness of breath or vertigo during the training. All patients should try to maintain their pre-experimental daily routine and dietary habits and be prohibited from participating in other regular exercises. The patient’s daily activities, diet and, rest habits will be understood through regular questionnaires and telephone interviews.

(1)Yijinjing exercise protocol

The patients will be taught by a dedicated rehabilitation therapist for 24 weeks, with a learning period for the first 4 weeks and an intensive training period for the last 20 weeks, practicing 3 times a week (Mondays, Wednesdays and Fridays) for 30 minutes each time, with a 5 minutes warm-up and relaxation.

Yijinjing exercise consists of 12 movements. Its intensity is quantified by the target heart rate, which is monitored in real-time by the patient wearing a Polar heart rate belt. The target heart rate is based on a reserve heart rate of 60% to 70% for moderate intensity aerobic training. The specific algorithm for the target heart rate is^[15]^: target heart rate = reserve heart rate *(60% to 70%) + resting heart rate, reserve heart rate = 220 - age - resting heart rate.

(2)Treadmill exercises protocol

The intensity of treadmill exercises is still monitored by the target heart rate. Patients will wear a Polar heart rate belt and first performs an acclimatization run on the treadmill, followed by a formal run. The running speed is gradually increased, but the heart rate is generally controlled within the range of the target heart rate. If the patient’s heart rate is outside or below that range, the intensity of the exercise is reduced or increased as appropriate. The running time is 30 minutes, including a 5-minutes warm-up. Exercise frequency is 3 times/week (Monday, Wednesday, and Friday) for 24 weeks.

(3)Strength training protocol

The strength training consists of five movements: bridge exercise, plank, seated training, swiss ball wall squats and ball squats, see Figure 3A to E. Each movement will be repeated 10 to 15 times and practiced 3 times a week (Monday, Wednesday, and Friday) for 30 minutes each time for a total of 24 weeks. The training should be easy first and then difficult, and the exercise load should be controlled at the target heart rate, so that patients feel fatigue and slight muscle soreness. Patients will be instructed not to hold their breath with force and to pay attention to safety.

**Figure 3. F3:**
[figure not shown]
Strength training protocol. (A) Bilateral bridge. (B) Plank. (C) Seated training. (D) Swiss ball wall squats. (E) Ball squats.

(1)Bilateral bridge

The bridge exercise is based on an unstable support surface. The patients are placed in the supine position, and the proximal ends of both lower legs are placed in the wide sling, and the trunk, knee, shoulder, and hip joints are maintained in the same line by raising the hips and extending the hips, and the movement lasts for 10 seconds.

(2)Plank

The patients are placed in a prone position, with both elbows bent over the bed, and the proximal ends of both lower legs set into the wide sling, then the body leaves the bed, ensuring that the ankle, hip, shoulder and head remain in a straight line. the movement lasts for 10 seconds.

(3)Seated training

The patients sit on the swiss ball with the trunk neutral and both lower extremities naturally separated. The therapist instructs the patient’s pelvis to tilt and rotate anteriorly, posteriorly, left and right on the swiss ball, maintaining each position for 5 seconds.

(4)Swiss ball wall squats

The patients squat with the back against the Swiss ball and holds the movement for 15 seconds, followed by standing up. Each movement is repeated 10 to 15 times depending on the situation.

(5)Ball squats

The patients maintain a deep squat, holds the upper limb straight and lifts the gravity ball (2 kg) 15~20 times, paying attention to the sunken shoulder and squatting posture.

### 2.8. Outcome measures

The patients were tested for outcome measures before and at the end of treatment.

(1)Pain

The patient’s low back pain level is assessed by the visual analogue scale.^[16]^ The score ranges from 0 to 10, with higher scores indicating greater pain.

(2)Muscle strength

Muscle strength is evaluated by grip strength of both upper limbs and isometric muscle strength of the trunk, hip and knee joints. Grip strength is assessed by an electronic grip strength meter. Isometric strength of the trunk and knee is evaluated by the Biodex system with a centripetal contraction mode. The test speeds are slow contraction (60°/s) and fast contraction (180°/s), and the test types are flexion and extension. The test sites were the left and right sides of the body, with no right or left side of the trunk. The outcomes include peak torque, average peak torque, average power, and peak flexor-to-extensor torque ratio.

(3)Balance

The static balance test will be conducted by the Italian Tecnobody balance system. Patients will stand with their right foot in the center of the pressure platform, then bend their left knee backward by 90° while crossing their hands at the waist, and tried to maintain standing with eyes open and eyes closed for 30 seconds each, with 15 seconds rest between groups. Static balance outcomes include the distance of plantar center of gravity pressure movement (mm), the area of movement trajectory (mm^2^), the deviation of the center of gravity in the X-axis and Y-axis (mm), and the average movement speed in the anterior-posterior and left-right directions (mm/s).

(4)Bone mineral density

BMD will be measured by Dual-energy X-ray absorptiometry at lumbar spine 2-4(L_2-4_) and femoral neck.

(5)Bone metabolism

After fasting for more than 12 hours, 10 mL of blood will be drawn from elbow vein in the morning of the next day, and serum bone metabolism indexes will be measured using a fully automated enzyme-labeled immunoassay instrument. The serum bone metabolism indexes include parathyroid hormone, osteocalcin, 25-hydroxyvitamin D3 (1,25(OH) 2D3), type I procollagen aminoterminal peptide and type I collagen carboxy-terminal peptide.

### 2.9. Statistical analysis

Statistical analysis will be performed by SPSS 22.0. If the data conforms to the normal distribution, paired *t* test is used for intra-group comparison and an independent-sample *t* test for inter-group comparison; a non-parametric test is conducted when the data does not conform to normal distribution. Differences are considered statistically significant at *P* < .05.

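### Section 2.9 tests change within each arm at the same P < .05 as the randomised comparison, and does not say which result carries the efficacy conclusion

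*Protocol article*

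**What the plan says.** Section 2.9 of the protocol article names two kinds of comparison in one sentence. Normally distributed data get a paired t test within each arm: "test is used for intra-group comparison and an independent-sample". For the comparison of the arms, and for the fallback, the sentence goes on: "test for inter-group comparison; a non-parametric test is conducted when the data does not conform to normal distribution". One threshold follows for everything: "Differences are considered statistically significant at" P < .05. The article does not call the within-arm tests descriptive, and it does not name the between-arm test as the basis for an efficacy conclusion.

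Other sections bear on what a within-arm change means in this trial:

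- **Section 2.7.** Control patients receive medication and education: "The patients will be advised to take a calcium supplement" containing calcium and vitamin D, for 24 weeks. Section 2.7.1 gives the experimental arm the same background plus the exercise programme.
- **Section 2.4.** Patients who had medication and regular exercise in the previous 3 months are excluded.
- **Section 2.3.** Entry requires a pain score above 3 and below 7 on the visual analogue scale. Pain on that scale is also an outcome (section 2.8).
- **Section 2.8.** Outcomes are measured twice, before and at the end of treatment. The serum markers include a vitamin D measure and parathyroid hormone.

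**The concern.** A paired test asks whether an arm changed over 24 weeks. It does not ask whether exercise caused the change. Three influences act in both arms and stay in the within-arm change:

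- the supplement and education, which can plausibly move the vitamin D and parathyroid hormone markers;
- the natural course of symptoms;
- regression to the mean in pain, because patients enter only if one reading falls inside a window.

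Only the comparison with the control arm removes these.

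The trouble comes when the two within-arm P values are set side by side. A result below .05 in the exercise arm and above .05 in the control arm looks like a treatment effect, but it does not test the difference between the arms. In arms of 16 to 20 patients such splits are common even when both arms change by the same amount. Since both kinds of test meet the same P < .05 rule, section 2.9 gives no ground for preferring one when they disagree.

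**Working it through.** **The plan's own figures.** Section 2.5 reports that "the sample size estimation resulted in 34 participants", then: "Considering a 20% dropout rate, the finalized sample size was 40 individuals". It gives no effect size or SD, only that "Statistical efficacy analysis was performed based on a previous study", so the 34 cannot be reproduced. It serves here only to fix the numbers per arm at 1:1 allocation:

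- randomised: 40/2 = 20 per arm;
- calculated requirement: 34/2 = 17 per arm;
- after the stated 20% dropout: 40 × 0.8 = 32, or 16 per arm.

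**Other inputs.** The test level is two-sided 0.05 (sections 2.5 and 2.9). The true mean change is δ, in SDs of change, and is the same in both arms, so exercise has no effect. δ is an assumption and is varied from 0 to 1.0.

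**Formulas.** Let p be the power of the paired t test in one arm: noncentral t, n − 1 degrees of freedom, noncentrality δ√n. The arms are independent, so:

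- P(exercise arm significant, control arm not) = p(1 − p);
- P(exactly one arm significant) = 2p(1 − p).

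**Results.**

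| δ (SD) | p, n = 16 | exercise only | exactly one arm | p, n = 20 | exercise only | exactly one arm |
|---|---|---|---|---|---|---|
| 0 | 0.050 | 4.8% | 9.5% | 0.050 | 4.8% | 9.5% |
| 0.3 | 0.203 | 16.2% | 32.3% | 0.247 | 18.6% | 37.2% |
| 0.5 | 0.465 | 24.9% | 49.8% | 0.565 | 24.6% | 49.2% |
| 0.6 | 0.612 | 23.7% | 47.5% | 0.721 | 20.1% | 40.2% |
| 0.8 | 0.848 | 12.9% | 25.7% | 0.924 | 7.0% | 14.1% |
| 1.0 | 0.962 | 3.7% | 7.3% | 0.989 | 1.1% | 2.3% |

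For example, at n = 16 and δ = 0.5: 0.465 × (1 − 0.465) = 0.249. With 17 per arm, the exercise-only figures are 16.8%, 25.0% and 11.2% at δ = 0.3, 0.5 and 0.8.

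**Shape.** p(1 − p) is largest at p = 0.5, where it equals 0.25. That point falls at δ = 0.52 for 16 per arm, 0.51 for 17 and 0.46 for 20. The risk therefore rises from about 5%, peaks at 25%, and falls again once the change is large enough for both arms to reach significance.

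**Set against the between-arm test.** In 200,000 simulated trials per setting, a two-sample t test on the changes was significant in 4.9–5.1% of trials at every δ tried, with 17 or 20 per arm. At δ = 0.5 and 20 per arm:

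- the exercise-only pattern occurred in 24.5% of trials;
- it came with a non-significant between-arm test in 22.2% of all trials, which is about 91% of the times it occurred (22.2/24.5).

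For δ from 0.3 to 0.6 that share was 87–91%.

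**The case against.** The strongest reply is that the correct test is already in the plan. The sentence that introduces the paired tests also specifies an independent-sample comparison of the arms, and nowhere does the article say that efficacy will be read from within-arm results. When the misleading pattern arises with equal arms, the planned between-arm test will usually stand beside it showing no significant difference. A shared threshold is also not a statement that the tests rank equally, and a fuller protocol or analysis plan may say which one carries the conclusion.

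Most of this stands. A reader might infer that the trial intends to claim efficacy from significance in one arm and not the other, or that its planned comparison is invalid. The documents support neither. Silence on ranking in a condensed article would not be a finding by itself. What remains is something the article does state: within-arm significance tests, under the same rule as the randomised test. The Discussion (section 3) adds to the risk. It speaks of observing changes in outcomes and of showing that the programme works, without tying either to the contrast between arms.

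The size is also open to challenge. Nothing in the article ties δ to 0.5 SD, and that value sits almost at the worst case, so 25% must not be read as the expected risk. Nor is 25% directly comparable with 5%: near 0.5 SD the pattern is essentially all in favour of exercise, while the 5% counts errors in both directions. Finally, the pattern becomes an error only if someone concludes efficacy from it.

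**Conclusion.** The point holds as a risk of interpretation and should be corrected; it is not a defect in the randomised comparison. Section 2.9 plans within-arm significance tests that cannot isolate the effect of exercise, under the same P < .05 rule as the test that can, and leaves open which one decides.

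If significance in the exercise arm only were taken as efficacy, the false-positive risk per outcome would be about 5% with no change in either arm, at most 25% near 0.5 SD of common change, and 7–13% at 0.8 SD, for 16–20 patients per arm. It would be 5% if the between-arm test alone decided. These figures assume the same true change and SD of change in both arms, equal numbers of completers, and normally distributed changes. The article supplies no SD or expected change, so the size for any given outcome is unknown within that range.

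**What to change.** Amend section 2.9 in two respects:

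1. Rest every efficacy statement on the between-arm difference at 24 weeks, adjusted for the baseline value of the same outcome, and report it with its 95% CI.
2. Replace the within-arm tests, including any non-parametric version, with the mean change and its 95% CI in each arm. Label these as descriptive and give no P values.

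Possible wording: *Conclusions about efficacy will be based only on the difference between groups at 24 weeks, adjusted for baseline, with a 95% confidence interval. Changes within groups will be summarised as means with 95% confidence intervals and will not be tested.*

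The baseline values are already collected, so this needs no further patients, visits or measurements and no change in sample size. The adjustment uses one degree of freedom. The only real downside is that there will be fewer P values to report.

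### The between-arm test uses no baseline covariate although every outcome has a baseline value; it is valid, but ANCOVA would be more precise at almost no cost

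*Protocol article*

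**What the plan says.** Section 2.9 sets out the whole comparison. It opens with "If the data conforms to the normal distribution, paired" t tests within groups. It then gives an independent-sample t "test for inter-group comparison; a non-parametric test is conducted when the data does not conform to normal distribution". No covariate or other baseline adjustment appears, and the section does not say whether the between-group test takes 24-week values or changes from baseline.

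Section 2.8 supplies the baseline: "The patients were tested for outcome measures before and at the end of treatment". This covers pain, muscle strength, balance, bone mineral density and the bone markers.

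On size and design, section 2.5 says "A two-sided test was selected, α was set to 0.05", "Statistical power was set to 0.8", "the sample size estimation resulted in 34 participants" and "Considering a 20% dropout rate, the finalized sample size was 40 individuals". Section 2.6 says "patients will be randomly assigned to experimental and control groups based on a 1:1 ratio" and names no stratification factor.

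**The concern.** A baseline measurement of the same outcome is usually the best available predictor of its 24-week value. A t test on 24-week values makes no use of it, so stable differences between patients stay in the error term. A t test on changes uses it, but forces a slope of 1, which over-corrects when the correlation is modest. ANCOVA estimates the slope from the data.

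This matters most in a small trial. With 20 per arm and no stated stratification, a visible baseline gap on some outcome is likely, and section 2.9 gives no agreed way to deal with it. What is at stake is power and the credibility of a result seen beside such a gap. The validity of the trial is not in question.

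**Working it through.** **Inputs from the article.** Two-sided alpha 0.05, power 0.80, 34 participants (17 per arm), 20% dropout, 40 randomised (20 per arm), 1:1 allocation. Evaluable after dropout: 40 × 0.8 = 32, or 16 per arm.

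**Inputs assumed.** The correlation rho between an outcome's baseline and 24-week values is not given, so a range is shown. The effect size is not given either and is back-solved below. Variances are taken as equal at both times and in both arms.

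**The plan's own figure.** The 34 cannot be reproduced forwards without an effect size. Backwards, a two-sample t test with 17 per arm reaches 80% power at d = 0.99: noncentrality 0.99 × √(17/2) ≈ 2.89 on 32 df. Values of d from about 0.99 to 1.02 all give 34.

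**Variance of the treatment difference**, relative to a t test on 24-week values:
- changes: 2(1 − rho)
- ANCOVA: 1 − rho²

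| rho | ANCOVA vs 24-week values | Changes vs 24-week values | Changes vs ANCOVA |
|---|---|---|---|
| 0.3 | 0.91 | 1.40 | 1.54 |
| 0.5 | 0.75 | 1.00 | 1.33 |
| 0.7 | 0.51 | 0.60 | 1.18 |
| 0.9 | 0.19 | 0.20 | 1.05 |

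Below rho 0.5 a change-score test is worse than leaving baseline out.

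**Power with 16 per arm and d = 0.99.** The noncentrality is 0.991 × √(16/2) = 2.80, divided by the square root of the relative variance, on 30 df (29 for ANCOVA).

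| rho | 24-week values | Changes | ANCOVA |
|---|---|---|---|
| 0.3 | 77% | 63% | 81% |
| 0.5 | 77% | 77% | 88% |
| 0.7 | 77% | 94% | 97% |

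The ANCOVA column charges one df but not the variance added by estimating the slope. On average that factor is 1 + 1/(32 − 4) = 1.036. By simulation it takes about 1.5 points off at rho 0.3 and about half a point at rho 0.7. At rho 0.9, 0.19 × 1.036 = 0.197 against 0.20 for changes, so the two are practically equal there.

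**Chance imbalance with 20 per arm.** The SD of the baseline difference is √(2/20) = 0.316 outcome SDs. P(gap above 0.5 SD) = P(|Z| > 0.5/0.316 = 1.58) = 11%.

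**What a 0.5 SD gap does with no treatment effect** (simulation, 20 per arm). The expected shift is rho × 0.5 on 24-week values and (rho − 1) × 0.5 on changes.

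| rho | Shift, 24-week values | Shift, changes | Rejection, 24-week values | Rejection, changes | Rejection, ANCOVA |
|---|---|---|---|---|---|
| 0.5 | 0.25 | −0.25 | 8.6% | 8.4% | 4.9% |
| 0.7 | 0.35 | −0.15 | 11.3% | 7.2% | 5.0% |
| 0.9 | 0.45 | −0.05 | 11.8% | 5.8% | 4.9% |

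These rates are conditional on the gap. With no gap, the test on 24-week values rejects only 2.5%, 0.7% and 0.01% of the time at the same rho.

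**Normality switch.** With 20 observations, a Shapiro-Wilk test flagged a lognormal sample (sigma 0.5) in 53% of simulations. For data that skewed, which test is used is close to a coin toss.

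**The case against.** Several stronger readings are tempting, and the article does not support them.

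- **That the plan ignores baseline altogether.** True only if 24-week values are compared. Section 2.9 does not say, and the Discussion speaks of observing changes in pain, strength and balance, so change scores are a fair reading. For very stable outcomes, which bone density may be, a change-score test would lose little.
- **That the test is biased or invalid.** Under randomisation the unadjusted test is unbiased and keeps its 5% error overall. The raised rejection rates above hold only given a gap and are balanced by low rates when there is none.
- **That power is disastrously low.** At an assumed d of 0.5, 16 per arm gives 28% on 24-week values against 88% with ANCOVA at rho 0.9. That d is about half what the sample size implies, and the contrast leaves out the change-score test, which has 86% in the same setting.
- **That the normality switch inflates error.** The rule is stated in advance and no inflation has been shown. The point is only that the test and the effect measure would depend partly on chance.

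It is also fair to say that an article condenses a protocol and that a SAP may add covariates. This carries limited weight: section 2.9 states a method, so the choice has been made and is open to comment. Finally, entry restricts pain to scores between 3 and 7, which probably lowers rho and the gain for that outcome.

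**Conclusion.** The point stands as one of efficiency. ANCOVA has the smaller variance on either reading of section 2.9 across the range shown, with near-equality to a change-score test at rho 0.9. Against a test on 24-week values, the variance falls by 9% at rho 0.3, 25% at 0.5, 49% at 0.7 and 81% at 0.9 (one minus the ratios in the first table). At the implied effect and 16 per arm, 24-week values give 77%, short of the planned 80%. ANCOVA is at about 80% at rho 0.3 and clearly above it from rho 0.5. It also deals with chance baseline gaps by a rule fixed in advance.

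The direction of the gain is secure. Its size rests on rho, which the article does not give and which will differ by outcome, and on the back-solved d of 0.99. The change is worth making, but the analysis as written is not invalid without it.

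**What to change.** In section 2.9, replace the between-group t test for each outcome with an ANCOVA: 24-week value as response, arm and that outcome's own baseline value as terms, reported as the adjusted difference with its 95% CI.

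State the model in advance instead of letting a normality test choose it. For skewed outcomes that are strictly positive, pre-specify a log transform. For outcomes that may be signed, such as the X- and Y-axis deviations, a log transform is unsuitable; keep the ANCOVA and add a rank-based ANCOVA as a sensitivity analysis. Sex may be added as a covariate, but this is optional.

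The cost is one degree of freedom (two if sex is included) and a change of wording. No new data are needed, and SPSS fits the model.
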